## Abstract

**Background::**

There are some clinical reports on dysphagia in patients with chronic obstructive pulmonary disease (COPD); however, its pathophysiology remains largely unknown.

Changes in respiratory function occur in patients with COPD causing a decrease in tidal volume and an increase in respiratory rate (tachypnea). In addition, it leads to lack of coordination between respiration and swallowing.

A new treatment called nasal high flow (NHF) has been introduced for patients with COPD, replacing the traditional non-invasive ventilation (NIV) procedure. The NHF therapy involves inhalation of high flow of humidified air, which reduces respiratory effort in patients with COPD. Furthermore, NHF therapy facilitates swallowing of saliva even during respiratory management. A recent clinical study reported that high-flow nasal cannula oxygen therapy for 6 weeks improved the health-related quality of life and reduced hypercapnia in patients with stable COPD. Taken together, NHF therapy is gaining attention in the clinical management of patients with COPD.

Therefore, in this study, we aim to examine the efficacy of NHF therapy on the coordination between breathing and swallowing of saliva during daytime nap in patients with COPD.

**Methods/Design::**

This open-label, investigator-initiated, single center study will evaluate the efficacy of NHF therapy on the coordination between breathing and swallowing of saliva during the daytime nap in COPD patients with forced expiratory volume in 1 second (FEV_1_%) of <70% during treatment at the Nagasaki University Hospital Respiratory Rehabilitation Center. Evaluations will be performed during the 90 to 180 minute “daytime nap” in the measurement room of the hospital. The primary endpoint will be the rate of appearance of the expiratory phase after swallowing of saliva and the frequency of swallowing during the measurement period.

**Discussion::**

The purpose of this study is to obtain evidence regarding the utility of NHF as a potential therapeutic device for COPD patients to prevent aspiration of saliva during the sleep stage of daytime nap. The utility will be assessed by comparing the decrease in incidence rates of the expiratory phase after swallowing of saliva in the NHF device group and the control group, wherein this device was not used.

## Introduction

1

There are some clinical reports on dysphagia in patients with chronic obstructive pulmonary disease (COPD)^[1]^; however, its pathophysiology remains largely unknown.^[2]^ Changes in respiratory function occurs in patients with COPD causing a decrease in tidal volume and an increase in respiratory rate (tachypnea). In addition, it leads to lack of coordination between respiration and swallowing, as well as a delay in the induction of the swallowing reflex. Studies have suggested that factors such as dyspnea associated with swallowing and lung hyperinflation may cause dysphagia.^[3]^

Coordinated movements of muscle groups related to breath-holding, such as the diaphragm and rectus abdominis, are important to control normal apnea during swallowing. The coordination between swallowing and respiratory movements may be impaired due to dysfunction of the breath-holding muscles and changes in lung capacity in COPD patients with a hunched posture. However, to date, the nature of the inhibition in coordination between swallowing and respiratory movements caused by changes in respiratory function in COPD patients has not been clarified.

Furthermore, aspiration of saliva during sleep as well as on awakening has been recognized as a major problem. The breathing pattern of an individual changes during the non-rapid eye movement (REM) and REM sleep periods, wherein the muscles of the pharynx relax, which may increase the risk of salivary aspiration compared with that during awakening.

The forward leaning posture with fixed upper limbs in patients with COPD increases the efficiency of the accessory respiratory muscles, namely the oblique and sternocleidomastoid muscles. The preliminary expiratory volume decreases as the degree of inspiration increases, comprising an increase in the index of kyphosis in order to compensate for chronic lung hyperinflation, exhalation restriction and weakness of the expiratory muscles.

Apnea is important to prevent aspiration during swallowing, and muscle functions related to breath-holding in the expiratory phase are considered to be easily affected by lung volume fractionation due to postural changes. We argue that, in order to control normal swallowing apnea, coordinated movements of muscle groups such as the diaphragm and rectus abdominis related to breath-holding are important; however, COPD is accompanied by changes in the dorsal-posterior posture of the patients. Therefore, we hypothesize that the coordination between swallowing and breathing movements is impaired due to dysfunction of the breath-holding muscles and the change in lung capacity.

A new treatment called nasal high flow (NHF) has been introduced for patients with COPD, replacing the traditional non-invasive ventilation (NIV) procedure. The NHF therapy involves inhalation of high flow of humidified air, which reduces respiratory effort and reduces respiratory function in patients with COPD.^[4–6]^ In addition, a study revealed that NHF therapy improved the respiratory work in patients during sedation with anesthetics.^[7]^ Furthermore, NHF therapy facilitated swallowing of saliva even during respiratory management.^[8,9]^ In a recent clinical study, Nagata et al^[10]^ reported that high-flow nasal cannula oxygen therapy for 6 weeks improved the health-related quality of life and reduced hypercapnia in patients with stable COPD. Nagata et al^[10]^ also conducted a multicenter randomized controlled trial to investigate the efficacy and safety of long-term high-flow nasal cannula oxygen therapy in stable COPD patients. Taken together, NHF therapy is gaining attention in the clinical management of patients with COPD.

Therefore, in this study, we aim to examine the efficacy of NHF therapy on the coordination between breathing and swallowing of saliva during the daytime nap in patients with COPD. This is an original research to test the preventive ability of NHF therapy in aspiration of saliva occurring during the daytime nap in patients with COPD (Fig. 1).

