### Outcome

2.7

The primary endpoint will be the frequency of swallowing of saliva during the measurement period and the rate of appearance of the expiratory phase.

The secondary endpoints will be: time-weighted average value of TcPO_2_ (average partial pressure during the observation period), time-weighted average value of TcPCO_2_ (average partial pressure during the observation period), time-weighted average value of SpO_2_ (average oxygen saturation during the observation period), time-weighted average respiratory rate (average respiratory rate during the observation period).

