## Discussion

3

Aspiration pneumonia due to dysphagia, which has been reported to occur due to dysfunction of the breath-holding muscles, is often observed in COPD patients with postural changes. However, there is lack of clarity regarding the pathophysiology of the respiratory function affected by aspiration pneumonia caused by dysphagia in such patients. It has been reported that aspiration pneumonia due to dysphagia often occurs in patients with COPD, and dysphagia is observed in approximately 9% of the patients; however, its pathophysiology is unknown. Moreover, there is no established treatment for dysphagia in patients with COPD.^[3]^ Furthermore, spinal deformities, such as a dorsal posture, are often observed in such patients to compensate for respiratory disorders. Deterioration of respiratory function due to such postural changes can interfere with respiratory coordination during swallowing. Changes in respiratory function occur in patients with COPD causing a decrease in tidal volume and an increase in respiratory rate (tachypnea). In addition, it leads to lack of coordination between respiration and swallowing. It has been suggested that factors such as dyspnea associated with swallowing and lung hyperinflation may cause dysphagia.^[15]^ Coordinated movements of muscle groups related to breath-holding, such as the diaphragm and rectus abdominis, are important to control normal apnea during swallowing. However, patients with COPD may have a hunched posture resulting in lack of coordination between the breath-holding muscles. Coordination between swallowing and respiratory movements may be impaired due to muscle dysfunction, changes in lung capacity, and dyspnea.

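### The article says the trial tests prevention of saliva aspiration, but its endpoints measure only breathing-swallowing coordination and gas exchange; the stated purpose should be limited to coordination.

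*Protocol article*

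**What the plan says.** The protocol article describes what the study is for in two ways.

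- **Coordination.** The abstract's Background and Methods/Design, and the end of section 1, give an effect on coordination as the aim: "we aim to examine the efficacy of NHF therapy on the coordination between breathing and swallowing of saliva during the daytime nap".
- **Aspiration.** The next sentence of section 1 goes further: "This is an original research to test the preventive ability of NHF therapy in aspiration of saliva occurring during the daytime nap". The Discussion part of the abstract says the purpose is "to obtain evidence regarding the utility of NHF as a potential therapeutic device for COPD patients to prevent aspiration of saliva", and then how this will be judged: "The utility will be assessed by comparing the decrease in incidence rates of the expiratory phase after swallowing of saliva".

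Section 2.7 sets the outcomes. "The primary endpoint will be the frequency of swallowing of saliva during the measurement period and the rate of appearance of the expiratory phase". Four time-weighted averages serve as secondary endpoints: TcPO2, TcPCO2, SpO2 and respiratory rate. Section 2.8 repeats the same measures for efficacy.

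Section 2.5.5 explains why the respiratory phase matters: moving to exhalation after a swallow protects the airway, and swallowing during inspiration may allow aspiration. Sections 2.1 and 2.11 call the study exploratory. It will report differences or ratios with 95% confidence intervals, and the estimates will be used to size a verification study.

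**The concern.** A statement that a trial tests prevention of an event implies that the event, or an accepted indicator of it, is observed under each condition. Here it is not. A favourable difference in respiratory phase after swallowing would be evidence about the first step of a two-step argument (NHF changes coordination; better coordination reduces aspiration). The second step is taken from the rationale and not examined.

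What is at stake is the conclusion that the trial may draw. With the purpose worded as it is, a change in the surrogate could be read as evidence that aspiration was prevented. The ambiguity could also carry forward, because section 2.11 feeds these estimates into the sample size of the verification study. Whoever designs that study needs to know whether they have an effect on coordination or an effect on aspiration.

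**Working it through.** The plan gives no figure to reproduce on this point. The check sets the stated purpose against what is measured.

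1. **Stated target.** Section 1 (second sentence of the aim) and the abstract's Discussion name prevention of saliva aspiration.

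2. **Endpoints, from sections 2.7 and 2.8.**
   - Swallow frequency: counts swallows, not aspiration.
   - Expiratory phase after a swallow: classifies breathing phase, not aspiration.
   - TcPO2, TcPCO2 and SpO2: gas exchange averaged over the observation period; no event is identified.
   - Respiratory rate: averaged likewise; no event is identified.

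   Count: 2 primary components + 4 secondary endpoints = 6, of which 0 detect aspiration.

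3. **Other measurements.** Section 2.5.1 has MWST, RSST and cervical auscultation performed in all patients. None is listed as an endpoint, none is placed within the nap, and the article defines no aspiration event from them. EMG, the sleep recordings and the kyphosis index do not detect aspiration either. So nothing measured elsewhere fills the gap as the article stands.

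4. **Link from surrogate to target.** Section 2.5.5 says that aspiration may follow a swallow in inspiration. That is a conditional statement of mechanism. The article gives no figure for how much aspiration would change with a given change in post-swallow phase, so a difference in phase cannot be converted into an amount of aspiration prevented.

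5. **What the design does answer.** Each patient is measured during a nap with NHF and a nap without it, at least 1 week apart (section 2.5.6). The difference or ratio in the two primary components, with its 95% confidence interval (section 2.11), estimates the immediate effect on coordination. This matches the coordination aim exactly.

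The aspiration wording is therefore the part that has no matching measurement. One related detail in the same part of the abstract also needs attention: it speaks of a decrease in the expiratory phase after swallowing, whereas section 2.5.5 treats the shift to exhalation as protective. The two must be reconciled when the sentence is rewritten.

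**The case against.** The best defence has four parts.

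- The formal aim is coordination, it stands immediately before the disputed sentence, and the primary endpoint measures it. **This stands.** A reader might infer that no result could meet the study's purpose. The documents do not support that: the coordination aim can be met, and the result would also be indirect evidence bearing on aspiration.
- The abstract is hedged (utility, potential device) and says openly that respiratory phase is the yardstick. **This stands in part.** Disclosing the yardstick makes the surrogate visible, but the abstract still names aspiration prevention as the purpose and does not say that the conclusion stops at the surrogate.
- The study is exploratory and sets no hypothesis test or success rule for aspiration. **True**, and it means that one cannot say a positive result will be reported as prevention. It is also a reason not to describe the study as a test of preventive ability.
- A journal article leaves detail to the full protocol. **True of detail**, but the purpose and endpoints are stated here and do not match.

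Four further readings go beyond the documents.

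- Section 3 speaks of preventing silent aspiration, but as the goal of using the device, through better coordination. That is rationale, not the trial's purpose.
- The surrogate cannot be called unvalidated from this text, because the cited method papers are not shown.
- Section 3 says "dysphagia is observed in approximately 9% of the patients; however, its pathophysiology is unknown". One might compute 15 × 0.09 = 1.35 expected patients with dysphagia and 0.91^15 = 0.243 for the chance of none, and infer that there is little to correct. That does not follow. Dysphagia is not the same as incoordination, which the article attributes to COPD and posture generally, and every patient's saliva swallows contribute to the primary endpoint. The target group also needs oxygen and is likely to differ from the population behind the 9%. At an assumed prevalence of 5% to 30%, the chance of none runs from 46% to 0.5%.
- The total NHF observation of at most 15 × 3 h = 45 h proves nothing by itself, because the article gives no aspiration rate to set against it.

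**Conclusion.** The point holds as one about claim and conclusion. In two places, section 1 and the abstract's Discussion, the article states a purpose of testing or giving evidence on aspiration prevention, while 0 of 6 endpoints detect aspiration. The trial can estimate only an effect on breathing-swallowing coordination, tied to aspiration by a mechanism the article describes as possible.

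It does not invalidate the coordination estimate, the crossover comparison or the planned intervals, and it does not require selecting patients with dysphagia. The verdict assumes that the endpoint list in sections 2.7 and 2.8 is complete. If the full protocol names an aspiration measure, the remedy would be to state it in the article instead. The change is worth making because it determines what the trial may conclude and costs almost nothing.

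**What to change.** In section 1 and in the Discussion part of the abstract, replace the aspiration wording with a purpose such as: to estimate the immediate effect of NHF on breathing-swallowing coordination during a daytime nap in patients with COPD, measured by how often expiration follows a saliva swallow and by swallow frequency. Add that these measures are a surrogate and that no conclusion on prevention of aspiration will be drawn. In the same edit, make the favourable direction of the expiratory-phase measure agree with section 2.5.5.

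Section 3 may keep its sentence on silent aspiration as the rationale for the device.

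Optionally, report how many patients have abnormal MWST, RSST or cervical auscultation results, as context only. The number may be very small, so no comparison by that status should be relied on.

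The cost is wording, plus at most one descriptive count from data already collected. The downside is a more modest headline claim.

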**Figure 1 F1:**
[figure not shown]
There are at least 3 factors affecting the coordination between swallowing and respiration during sleep stage. Increase in respiratory rate and decrease in tidal volume due to COPD. Deformation of the spinal column and the change in respiratory function caused by the dorsal posture. Decrease of muscle activity during sleep and posture change. Therefore, inhibitory effect on saliva swallowing by altered coordination between swallowing and respiration might occur silent aspiration during sleep. The application of nasal high flow with air could prevent “silent aspiration” by improving respiratory function during sleep stage in COPD patients. COPD = chronic obstructive pulmonary disease.

## Methods/design

2

### Study design

2.1

The present study has been designed in accordance with the Standard Protocol Items: Recommendations for Interventional Trials and Consolidated Standard of Reporting Trials 2010 guidelines.^[11,12]^

This is an open-label, investigator-initiated, single center study on the efficacy of NHF therapy in COPD patients during the daytime nap as shown in Fig. 2.

**Figure 2 F2:**
[figure not shown]
After obtaining informed consent, subjects who meet the registration requirements will be randomly assigned to either of the 2 groups. Fifty-percent of the patients will be randomly assigned to each group for this crossover study. The experimental group will be Oxygen therapy group with NHF application (40 L/m with air + 5 L O_2_ FiO_2_ = 0.3), control group will be Oxygen therapy group with nasal cannula (3 L/m oxygen FiO_2_ = 0.3).

The primary endpoint will be the occurrence rate of the expiratory phase after swallowing of saliva.

The Clinical Research Review Board of Nagasaki University has approved the study protocol. The study will be conducted at Nagasaki University Hospital in Japan. The study is registered in the jRCTs. The study will be conducted in accordance with the principles of the Declaration of Helsinki and the established best clinical practices of Japan. This is an exploratory study aimed at collecting information for conducting a verification study. Therefore, the number of cases will be set based on the feasibility in our hospital.

### Participant recruitment

2.2

Participants will be recruited from the Nagasaki University Hospital, where the subsequent study will also be conducted. The treating clinical research coordinator (CRC) will explain the study to the recruited individuals, and an informed consent form will be signed by those who agree to participate. This is a randomized crossover study, and will comprise 2 groups of patients. Both groups will be tested during the daytime nap, and the NHF device will be used concomitantly in 1 group.

After obtaining consent, subjects who meet the registration requirements will be randomly assigned to either of the 2 groups. Fifty-percent of the patients will be randomly assigned to each group for this crossover study as shown in the figure below.

Fifteen patients with stable COPD, aged 40 years or older, who need oxygen therapy and show FEV_1_% of <70% will be recruited from the Nagasaki University Hospital Respiratory Rehabilitation Center. Patients with hypercapnia due to COPD (arterial blood carbon dioxide partial pressure [PaCO2 ≧ 45 Torr]) in the stable period, history of exacerbation of COPD (moderate or higher) in the past year, and those requiring home oxygen therapy will also be recruited. Patients with hypercapnia due to COPD (arterial blood carbon dioxide partial pressure [PaCO2 ≧ 45 Torr]) in the stable period, history of exacerbation of COPD (moderate or higher) in the past year, and those requiring home oxygen therapy will also be recruited.

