### Study protocol

2.5

Evaluations will be performed during the 90 to 180 minute “daytime nap”^[13,14]^ in the measurement room of the Department of Anesthesiology and Biomedical Administration, Nagasaki University Hospital.

COPD patients, as an allocation factor, will be classified into 2 groups, a stage 2 group (80% ≧ FEV_1_ > 50%) and a stage 3 group (50% ≧ FEV_1_ > 30%), according to severity based on the standard FEV_1_.

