#### Measurement of the index of kyphosis

2.5.6

Curvature of the spine from the 7th cervical vertebra to the 4th lumbar spinous process will be considered for quantitative evaluation of kyphosis using an 80 cm long flexible curved ruler (made by Shinwa) in an easy sitting position with no plantar contact. The shape will be traced on the paper as a straight line L (cm) connecting the seventh cervical and the fourth lumbar spinous processes of the curve. The distance from the straight line L to the apex of the curve will be H (cm), based on the formula by Milne et al.^[14]^ The ratio will be calculated as the index of kyphosis.

We will administer NHF (30–40 L/min of air and 5 L of oxygen [FiO_2_ = 0.3]) during nap sleep, in order to assess the immediate effect of the therapy on swallowing function in patients with COPD. Assess swallowing function. On the first measurement day, patients will be randomly allocated to either the high-flow nasal cannula oxygen therapy group or the no NHF therapy group with only oxygen (3 L oxygen [FiO_2_ = 0.3]) group (1:1). The second crossover measurement will be performed at least 1 week after the first with reversal of treatments in the 2 groups. In both groups, oxygen will be administered by a nasal cannula at a flow rate sufficient to cause an increase in PaO_2_ to over 60 mm Hg (oxygen saturation >90%, usually ≤3 L/min at rest). Patients with hypercapnia due to COPD (arterial blood carbon dioxide partial pressure [PaCO2 ≧ 45 Torr]) in the stable period, history of exacerbation of COPD (moderate or higher) in the past year, and those requiring home oxygen therapy (COPD GOLD stages 2 and 3) will be the target cases.

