### Statistical analyses

2.11

Considering the exploratory nature of this study, we will estimate the incidence rate for each study parameter and use the information to calculate the necessary sample size for the verification study, in order to achieve statistical significance.

Specifically, the rate of appearance of the expiratory phase after swallowing of saliva and the frequency of swallowing during the measurement period in the NHF device and control groups will be calculated. The difference (ratio) between the 2 groups and the 95% confidence interval on both sides will be calculated. For other items, the average value and standard deviation for each group will be calculated manually.

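### Section 2.11 does not use the randomised order of the crossover, so a change between sessions makes the NHF interval too wide and, with unequal orders, shifts the estimate

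*Protocol article*

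**What the plan says.** - **Design.** Section 2.2 calls the study a randomised crossover and states "Fifty-percent of the patients will be randomly assigned to each group for this crossover study as shown in the figure below". The number is in the same section: "Fifteen patients with stable COPD, aged 40 years or older, who need oxygen therapy". Section 2.1 explains its basis: "the number of cases will be set based on the feasibility in our hospital".
- **Sessions.** Section 2.5.6 gives 1:1 allocation to the treatment of the first measurement day, then: "The second crossover measurement will be performed at least 1 week after the first with reversal of treatments in the 2 groups".
- **Allocation factor.** Section 2.5: "COPD patients, as an allocation factor, will be classified into 2 groups", namely GOLD stage 2 and stage 3. The article does not say whether allocation is simple, blocked or minimised.
- **Primary contrast.** Section 2.11 first says that the rate of post-swallow expiration and the swallowing frequency will be calculated under NHF and control. It continues: "The difference (ratio) between the 2 groups and the 95% confidence interval on both sides will be calculated". Order, session and pairing within patient are not mentioned.

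**The concern.** In a two-session crossover each patient gives one NHF-minus-control difference. For patients who have NHF first, a change from session 1 to session 2 is subtracted from that difference. For patients who have it second, the change is added. Two things follow if the contrast ignores order.

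First, the session change enters the patient differences with opposite signs in the two orders. It is counted as random variation and widens the interval. Second, if the orders are unequal in size, the opposite signs do not cancel fully and part of the session change is reported as NHF effect.

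Some session change is plausible. The first session is the patient's first study nap with surface EMG, chest and abdominal bands, a transcutaneous electrode and EEG. The abstract also places recruitment "during treatment at the Nagasaki University Hospital Respiratory Rehabilitation Center". The documents report no such change and no size for one. The study exists to inform the planning of a verification study, so imprecision that could be removed at almost no cost is worth removing.

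**Working it through.** There is no power calculation to reproduce, because the sample size is a feasibility figure. The check concerns how the contrast behaves.

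**Inputs**
- N = 15 (section 2.2), allocated 50% or 1:1 (sections 2.2 and 2.5.6). 15 × 0.5 = 7.5, so the nearest split is 8:7.
- Session effect π (session 2 minus session 1), in units of the SD of the within-patient difference. It is not in the documents; the assumed range is 0 to 1.
- Allocation method: not in the documents.

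**Leak into the estimate.** Let τ be the NHF effect, n1 the number with NHF first and n2 the number with NHF second. The mean difference is τ − π in the first order and τ + π in the second. The unadjusted paired mean therefore estimates τ + π(n2 − n1)/N. The fraction of π that leaks is:
- 8:7: 1/15 = 6.7%
- 9:6: 3/15 = 20%
- 10:5: 5/15 = 33%

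**How often larger imbalances arise**
- Under simple randomisation, Binomial(15, 0.5): P(8:7) = 0.39, so an imbalance of 3 or more has probability 1 − 0.39 = 0.61. P(10:5 or worse) = 0.30.
- Under blocks of 4 within stage, with strata of 9 + 6 or 10 + 5 (assumed), 9:6 arises in about 17% of trials. The stratum with two patients in its last block is off by 2 with probability 1/3. The other stratum is off by 1 in the same direction with probability 1/2. 1/3 × 1/2 = 1/6.
- Dropout changes both terms. From 8:7, losing two patients from the smaller order gives 8:5 and a leak of 3/13 = 23%.

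**Width of the interval.** Without a session term, the expected variance of the differences is 1 + π² × (4·n1·n2/N²) × N/(N − 1).
- 8:7: 4 × 8 × 7/225 × 15/14 = 1.067, so the variance is inflated by 27% at π = 0.5 and by 107% at π = 1.
- 8:8, N = 16: 1 × 16/15 = 1.067, the same inflation. An even N does not remove it.

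The simulation used 100,000 trials per row, with the SD of the differences set to 1. It compares the paired t interval without a session term (14 df) with the session-adjusted interval (average of the two order means, pooled within-order variance, 13 df):

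| Split | π | Bias, unadjusted | Half-width, unadjusted | Coverage, unadjusted | Half-width, adjusted |
|---|---|---|---|---|---|
| 8:7 | 0 | 0.00 | 0.543 | 95.1% | 0.548 |
| 8:7 | 0.25 | 0.02 | 0.562 | 95.6% | 0.549 |
| 8:7 | 0.5 | 0.03 | 0.613 | 96.9% | 0.549 |
| 8:7 | 1 | 0.07 | 0.785 | 99.3% | 0.548 |
| 9:6 | 0 | 0.00 | 0.544 | 95.0% | 0.558 |
| 9:6 | 0.5 | 0.10 | 0.610 | 96.0% | 0.559 |
| 9:6 | 1 | 0.20 | 0.778 | 97.8% | 0.559 |
| 10:5 | 0 | 0.00 | 0.544 | 94.9% | 0.580 |
| 10:5 | 0.5 | 0.17 | 0.605 | 93.7% | 0.580 |
| 10:5 | 1 | 0.33 | 0.763 | 93.3% | 0.580 |

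The adjusted estimate showed no bias beyond simulation error, and coverage of about 95% in every row.

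- Excess width at 8:7: 0.613/0.549 = 1.12 at π = 0.5, and 0.785/0.548 = 1.43 at π = 1.
- Price of adjusting when π = 0: 0.548/0.543 = 1.01 at 8:7, 0.558/0.544 = 1.03 at 9:6, and 0.580/0.544 = 1.07 at 10:5.

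**The case against.** The strongest reply is that this is an omission which a condensed article may make. Section 2.11 never says that the contrast is unadjusted, and a session term is commonly left to an analysis plan, which is not shown. This stands in part: nobody can conclude from the article that the final analysis will lack the term. But section 2.11 is not merely silent. It specifies the primary contrast and interval, in wording that suits two parallel groups rather than a crossover. Correcting that wording is a change to text that is shown.

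The reply on size also largely stands. At 8:7 the bias is at most 0.07 SD over the assumed range, against a half-width of at least 0.54 SD. Coverage errs on the safe side and falls only to about 93% at 10:5. All of this rests on an assumed session effect in patients described as stable. Section 2.11 names estimated incidence rates as the input to the next sample size, not the width of this interval.

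Three stronger readings are tempting, and the documents do not support them:
- **That fifteen patients and a 50% split are a contradiction that spoils the comparison.** With an odd number, 50% or 1:1 is ordinary shorthand for 8:7, and the odd number does not cause the wider interval.
- **That serious imbalance is likely.** The 61% figure needs simple randomisation. The named allocation factor points towards something more restricted, though the method is not given.
- **That the data will be analysed as unpaired.** The wording allows that reading but does not state it. The point above holds even if the contrast is paired.

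**Conclusion.** The point holds in a limited form. As worded, section 2.11 does not use the randomised order. If the sessions differ, following it gives a worse interval than a session-adjusted contrast would. The main consequence is lost precision: at 8:7, about 12% excess width for a session effect of 0.5 SD and 43% for 1 SD, with almost none for 0.25 SD or less. Bias is secondary. It is negligible at 8:7 and becomes noticeable only if simple randomisation or dropout leaves the orders at 9:6 or worse. These figures assume a session effect between 0 and 1 SD and roughly normal within-patient differences; neither comes from the documents. The case for the change is that the remedy is nearly free, not that the planned result would be seriously wrong.

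**What to change.** In section 2.11, define the NHF effect for both primary measures as the within-patient contrast adjusted for session. That is the simple average of the two order-specific mean NHF-minus-control differences, with the 95% interval from the pooled within-order variance. This gives 13 df with 15 completers, and in general the number of completers minus 2. It is equivalent to a linear model with patient, session and treatment.

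Two details need stating with it. One is the scale on which the ratio is estimated, for example the log scale. The other is a rule for naps with zero swallows, where the expiratory-phase rate is undefined and the log of the frequency does not exist. A rate of zero raises the same problem on the log scale. The interval is normal-theory, so its use for a bounded proportion in fifteen patients should be acknowledged as approximate.

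As a minor clarification, sections 2.2 and 2.5.6 and the Figure 2 legend can give the allocation as 8:7 between the two orders, as balanced as possible within stage.

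The cost is one degree of freedom (14 to 13) and an interval about 1% wider at 8:7 or 3% at 9:6 if there is no session effect (about 7% if the split ends at 10:5). A few sentences change, with no extra patients or procedures.
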